**Figure 1 figure1:**
[figure not shown]
Flowchart of the study procedures. 360cc: 360 Concussion Care; ED: emergency department; MRI: magnetic resonance imaging; PQ: patient questionnaire.

### Study Setting

The study will be conducted at the Children’s Hospital of Eastern Ontario (CHEO) and the 360 Concussion Care (360cc) clinic, a tertiary health care concussion clinic. The neuroimaging component of the study will be completed at the Royal Ottawa Mental Health Centre’s Brain Imaging Centre on a 3-Tesla Siemens magnetic resonance-positron emission tomography system with a 32-channel head coil (Siemens Biograph mMR, Siemens).

### Eligibility Criteria

#### Inclusion Criteria

Adolescents presenting to either CHEO’s emergency department (ED) or 360cc after sustaining a direct or indirect mild traumatic brain injury (TBI) will be eligible to participate in this study if they (1) are aged 12 to <18 years; (2) have a diagnosed concussion (by a physician), (3) presented to the ED or 360cc within 7 days of TBI; (4) have a score >4 on the Predicting and Preventing Post-Concussive Problems in Pediatrics (5P) clinical risk score, a prediction rule to identify those at risk of poorer outcomes at 4 weeks postinjury [2]; and (5) are proficient in English [38]. To increase the probability of including adolescents with a true concussion, the adapted version of the American Congress of Rehabilitation Medicine [39] framework will be used [40]. Those with either 1 *highest level of certainty* symptom (dazed, confused, or trouble thinking within minutes after injury, difficulty remembering what happened just before or minutes after injury, and loss of consciousness) or 2 *higher level of certainty* symptoms (nausea or vomiting, headache, dizziness, clumsy or balance problems, blurred or double or change in vision, difficulty concentrating, and sensitivity to light or noise) immediately or within 1 hour of injury will be included.

#### Exclusion Criteria

Patients will be excluded if they present with TBIs with any of the following: (1) a Glasgow Coma Scale score of ≤13; (2) abnormality on standard neuroimaging studies [41], including positive head computed tomography findings (neuroimaging is not required, but may be performed if clinically indicated); (3) neurosurgical operative intervention, intubation, or intensive care required; (4) multisystem injuries with the treatment requiring hospital admission, operating room, or procedural sedation in ED (hospital admission for observation or management of ongoing concussion symptoms is not an exclusion criteria); (5) severe chronic neurological developmental delay resulting in communication difficulties; (6) intoxication to alcohol or drugs at the time of ED presentation as per clinician judgment; (7) no clear history of trauma as primary event to the concussion (eg, seizure, syncope, and migraine); (8) prior psychiatric hospitalization; (9) inability to obtain written informed consent or assent (eg, language barrier); (10) legal guardian not present (certain forms need to be completed by parents or legal guardians); (11) no internet and mobile or tablet access; and (12) currently in therapy.

In addition, patients will not be included in the magnetic resonance imaging (MRI) component if they present with the following: (1) previous neurological or neurodevelopmental disorder such as epilepsy, intellectual disability, or autism (history of attention-deficit or hyperactivity disorder or learning disability is not exclusionary); (2) previous stroke or transient ischemic attacks; (3) sedation medication (eg, propofol, ketamine, nitrous oxide, midazolam, benzodiazepines, and fentanyl) administered before or during ED visit; (4) inability to be present at the 72-hour (+48 or –48 hours) and 4-week (+5 or –5 days) MRI follow-up visits; and (5) medical contraindications to MRI (eg, claustrophobia, pregnancy, or presence of braces or spacers or other metal implants).

### Randomization, Blinding, and Allocation

#### Sequence Generation

The CHEO Clinical Research Unit will provide data management services for this study and retain randomization codes. The randomization sequence will be created using R software (version 3.1.1; R Foundation for Statistical Computing) [42] and will be stratified by sex, with a 1:1 allocation using random blocks.

#### Allocation Concealment

A statistician at the CHEO CRU (not involved in the study) will maintain the master list.

#### Implementation

The day after enrollment and once all questionnaire data are complete, research assistants (RAs) will call participants over the phone, and RAs will log into REDCap (Research Electronic Data Capture; Vanderbilt University) to obtain the patient’s group allocation. Only the RAs who randomized participants will be unblinded. The research team will be blinded to data acquisition. In case of a serious adverse event, the principal investigator and appropriate research staff will be unblinded to the participant’s group.

### Methods for Protecting Against Bias

The investigators, coaches, other research staff, data management staff, and biostatisticians will be blinded to the group assignment. Patients and families will be blinded to the purpose and expected results of the interventions and to the other treatment arm.

### Intervention Description

#### Experimental Group Description: MBI Training

To be delivered via the *AmDTx* platform (Figure 2), the targeted DTx MBI training consists of a 4- to 8-week custom-made program (containing 8-modules) for adolescents with concussion, including setting intentions and check-ins on mood and stress, audio-recorded lectures, guided meditations such as focused attention exercises, and journaling events (Table 1). Each standardized psychoeducation or meditation practice will be unlocked as the participant progresses through the MBI program. Participants will be encouraged to participate in the DTx MBI activities for approximately 10 minutes every day, for a minimum of 4 days a week, over the 4- to-8-week period. Those who choose to end their therapy on the fourth week will be immediately directed to module 8 *Reviewing the program and how to maintain practice*. Those who choose to continue for an additional 4 weeks will move on to modules 5 through 8. The curriculum is based on previously validated *AmDTx* MBI app protocols [27,43] and team expertise in youth MBI ([name], [name], MC, and [name]) and was peer reviewed by experts in the field and parent engagement leaders ([name], [name], and [name]). The intervention was piloted on 10 pediatric participants with concussion, and their feedback was integrated into the MBI and protocol [36]. We will track *meaningful* in-app use time, defined as the time spent engaging in meditation, psychoeducation, self-monitoring, and self-reflection, with a minimum threshold of 3 minutes per day. Any use time <3 minutes will not be counted toward the total weekly minutes spent using the *DTx.*

**Figure 2 figure2:**
[figure not shown]
Adolescent concussion dedicated experimental and control interventions delivered through the AmDTx platform. (A) Initial loading screen of AmDTx; (B) main menu or home screen of AmDTx as seen by the participants randomized to the experimental intervention; (C) journey selection screen. Concussion Journey is shown; (D) main or menu page of the concussion MBI. Slices of the badge are awarded upon the completion of each module; (E) main or menu page of module 1; (F) stage 1 of module 1 play screen; (G) to complete the stage, the participant taps on the arrows at the top right; (H) main or menu page of module 3, with participant progression up to stage 5. (I, J and L) Before and after each the participant is prompted to complete the wellbeing measurements “Snapshot”; (K) stage 4 of module 2, “Body Scan” preplay screen with 2 meditation guide options; (L) snapshot ecological momentary assessment for stress and the open field box features; (M) journaling feature menu; (N) journaling feature input page relating to goal setting; (O) main menu or home screen of AmDTx as seen by the participants randomized to the control intervention. The feature “Concussion Recovery” is where the control math game is found; (P) main screen of the control task; (Q) to ensure as much similarity in the experience as possible and to collect valuable insights into the well-being of participants, the control is also book-ended with snapshots. Shown here is the mood circumplex feature; (R) control task midway through completion; (S) timer message prompting the participant to end their cognitive training for the day; (T) snapshot selfie scan feature after video has been captured; (U) the My Insights page where the participants randomized to either group can view how individual intervention stages or the control task impacted their well-being.

**Table 1 table1:** Four- or 8-week experimental intervention consisting of a targeted digital therapeutics mindfulness-based intervention for adolescents with concussion that includes setting intentions and check-ins on mood and stress, audio-recorded lectures, guided meditations such as focused attention exercises, and journaling events.

Module	Course or focus	Meditation practices	Exercise
1	What is mindfulness Setting intentions Belly breathing exercise Introduction to body scan	Body scan (short): 7 minutes × 2 Belly breathing: 3 minutes × 2	N/A^a^
2	Mindful attitudes (nonjudgment and acceptance) How to skillfully meet concussion symptoms	Mindfulness of breath: 5 minutes × 2 Body scan: 15 minutes × 2	Setting goals Positive event journal Doing 1 daily routine mindfully
3	Stress response The biology of stress Inner narrative and chronic stress STOP technique	Mindful of breath: 10 minutes × 2 STOP technique Mindful movement: 7 minutes × 2	Symptoms of stress checklist and mapping stress on the body Journal when you used the STOP technique
4	Thoughts: the stories we tell ourselves Reframing symptoms with thoughts and attitudes Moving mindfully through your life	Mindfulness of sound transitioning to thoughts: 10 minutes × 2 Mindfulness movement: 10 minutes × 2	Thought journal
5	Pain and emotions How to mindfully manage pain Being mindful of your emotion The Breathe-Calm-Okay-Observe-Love technique	Body scan: 12 minutes × 2 Practice sitting meditation with emphasis on emotion: 10 minutes × 2	N/A
6	How to return to activities Gratitude—who or what has helped you in your recovery	Mindful movement practice: 10 minutes × 2 Loving-kindness and gratitude practice: 10 minutes × 2	Thought journal
7	Integrating mindfulness more fully into daily life Barriers to practice	Open awareness practice: 10 minutes × 2 Users choice practice: 5-15 minutes × 2	Thought journal
4 or 8	Review of program, strategies for maintaining practice, and reflection on how mindfulness has helped cope with your concussion or otherwise	Users choice practice: 5-15 minutes × 4	Review treatment goals Goal setting for the future

^a^N/A: not applicable.

#### Control Group Description: Sham App

To control for daily access to the *AmDTx* platform, expectation, and clinical attention bias, we created a sham DTx for the control group. The sham DTx will be delivered on the same main interface, within *AmDTx*; however, these participants will not have access to any of the MBI training or psychoeducational content. Their sham DTx will consist of playing an open-source math game called 2048 developed by Gabriele Cirulli [44]; this will be communicated to the control participants as *cognitive training*. The game requires participants to slide number tiles on a grid and combine them to create a tile with the number 2048. In a previous study, *AmDTx* was compared with 2048, revealing that 2048 did not reduce stress or improve psychological well-being in university students with anxiety [27]. Furthermore, 2048 was previously tested in a pediatric population with concussion, and the study found no evidence of harm or symptom improvement at 4 weeks [45]. It is expected that the control intervention will not bother individuals with sensitivity to light or high velocity motion because it lacks fast visuals or movement. The game is programmed to only be accessible for 10 minutes per day.

#### Coaching

All participants will be followed weekly by a coach through SMS text messaging. The coaches’ role will be to ensure that the participants adhere to the intervention. All the participants will receive weekly text messages from a coach. These messages will be sent on the same day and time every week and will be limited to 160 characters. The coaches will use a standardized question and answer protocol developed by the team. Coaches will also remind the participants to complete their follow-up surveys.

Furthermore, both interventions are equipped with automated reminders (triggered by inactivity).

#### Standard of Care

All the participants will receive standard of care [46] instructions pamphlet provided by RAs in the ED or at 360cc. The standard of care indicates that the patient refrains from physical and cognitive activities for 24 to 48 hours after injury. After the rest period, it is recommended that low-to-moderate levels of physical and cognitive activity be gradually started, including screen time. The activities should be performed at a level that does not result in the recurrence or exacerbation of symptoms. Adolescents must refrain from any activities that increase the risk of reinjury (eg, contact sports or anything with risk of falls) until fully asymptomatic and cleared by their primary care or other medical providers.

### Measures and Outcomes

#### Primary Outcomes

The prespecified thresholds (criteria for success), as outlined in Table 2 for the feasibility, are based on established benchmarks of previous feasibility trials [47,48] and our previous experience in recruiting pediatric patients with concussion from an ED [49]. We will use the *traffic light* system to determine whether proceeding to a full-scale trial is appropriate [50]. Progression can take place without any changes (green zone), with correctable adjustments (amber zone), or not occur because of issues that cannot be readily addressed (red zone). The decision to progress to a full-scale trial will be contingent on the criterion with the least favorable performance [50].

Table 3 provides an overview of all outcome measures collected and their specific end points.

**Table 2 table2:** The criteria for success for progression to a full-scale efficacy trial.

Feasibility outcomes	Green zone (go)	Amber zone (amend)	Red zone (stop)
Eligibility	>40% of participants screened are eligible	20%-40% of participants screened are eligible	<20% of participants screened are eligible
Recruitment	>50% of eligible participants will be randomized [49]	30%-50% of eligible participants will be randomized	<30% of eligible participants will be randomized
Adherence	>70% of participants complete the minimum requirements, that is, approximately 10 minutes of activity 4 times a week	>50% of participants complete the minimum requirements, that is, approximately 10 minutes of activity 4 times a week	<50% of participants complete the minimum requirements, that is, approximately 10 minutes of activity 4 times a week
Credibility^a^	>70% of participants have score above the scale midpoint	>50% of participant have a score above the scale midpoint	<50% of participants have a score above the scale midpoint
Retention	>75% participants complete the follow-up assessment [49]	50%-75% participants complete the follow-up assessment	<50% participants complete the follow-up assessment

^a^Treatment credibility and expectancy will be assessed using the Credibility and Expectancy Questionnaire [51]. It is a 6-item questionnaire, scored using a Likert scale ranging from 1 to 9. The treatment will be considered credible (questions 1-3) if the participants scored above the midpoint. Furthermore, credibility and expectancy will be assessed to rule out the possibility of differential credibility as an explanation for the differences in therapy outcomes between the experimental and control groups. The credibility and expectancy of the intervention will be assessed at 1 week after enrollment.

**Table 3 table3:** Measures organized by domain, source of data, and assessment occasion.

Measures				Source or reporter		Time to complete (minutes)		CHEO ED^a^		360cc^b^		Daily^c^		Day 1 (CHEO)		Day 1 (360cc)		72-hours		Day 7		Day 14		Week 3		Week 4		Week 8

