## Methods

### Trial Design

The proposed study is a Health Canada–regulated parallel-group (1:1) RCT, where patients within 7 days of a concussion will be randomly assigned to one of the two groups: (1) experimental group (n=35), early introduction of the DTx MBI program and (2) control group (n=35), sham DTx attention-matched comparator intervention. The participants will start the intervention the next day after being enrolled in the study. After 4 weeks, those in the experimental group will be offered the MBI program with 4-week additional education modules. Those who are part of the control group will be offered to cross over to start the DTx MBI. Of the 70 participants enrolled, 60 (86%) consenting participants (n=30, 50% from the experimental group and n=30, 50% from the control group) will be enrolled in neuroimaging, which requires participation in a brain scanning session within 72 hours of enrollment and during week 4 of the study. For a schematic diagram of the trial design, procedures, and stages, refer to the study flow diagram in Figure 1.

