**Outcomes**																												
	**Psychological**																											
		Self-Efficacy Questionnaire for Children	C		2-5								✓		✓										✓		✓	
		Connor-Davidson Resilience Scale	C		2-5								✓		✓										✓		✓	
		Generalized Anxiety Disorder 7-item scale	C		2-5		✓								✓										✓		✓	
		Center for Epidemiologic Studies Depression Scale for Children	C		2-5		✓								✓										✓		✓	
		Child and Adolescent Mindfulness Scale	C		2-5		✓								✓										✓		✓	
		Credibility Expectancy Questionnaire	C		5														✓									
		Client Satisfaction Questionnaire	CP		5																				✓			

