#### Secondary Outcomes

##### Treatment Expectancy

*Treatment expectancy* will be assessed with the Credibility and Expectancy Questionnaire (questions 4 to 6) [51]. Expectancy will be considered good if the participants score above the midpoint on questions 4 to 6. Expectancy will be assessed at 1 week after the enrollment.

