The day following the ED or 360cc visit, participants will receive a phone call from an RA to randomize the participants to either the experimental or the control group and give instructions to register an account on a study-dedicated landing page using a unique link for each participant. Following registration, participants will install *AmDTx* on the mobile device of their choice. After creating an account and logging in to *AmDTx*, each participant will be automatically directed to their assigned intervention (MBI or control).

During this phone call, an MRI appointment will be scheduled for the participants who have agreed to participate in that component of the study. Participants will complete the surveys or questionnaires for day 1 and MRI screener. They will have the option of completing the survey via phone or REDCap.

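### Credibility and expectancy are rated once, after about six days of app use, so a between-arm difference could not be read as a rival explanation of outcome differences

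*Protocol article*

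**What the plan says.** Footnote a to Table 2 (Measures and Outcomes, Primary Outcomes) sets the time: "The credibility and expectancy of the intervention will be assessed at 1 week after enrollment". The Treatment Expectancy section repeats it: "Expectancy will be assessed at 1 week after the enrollment". In Table 3 the row "Credibility Expectancy Questionnaire" carries one tick, which by column count falls under Day 7. No earlier rating is listed for either arm.

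The same footnote gives the questionnaire two uses. One is the feasibility criterion, the share of participants scoring above the midpoint. The other is "to rule out the possibility of differential credibility as an explanation for the differences in therapy outcomes between the experimental and control groups".

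On the start of treatment, Trial Design says: "The participants will start the intervention the next day after being enrolled in the study". Data Collection Methods describes the day-1 contact, at which "participants will receive a phone call from an RA to randomize the participants to either the experimental or the control group"; app registration and installation come after that. The encouraged use is "approximately 10 minutes every day, for a minimum of 4 days a week" (Experimental Group Description).

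**The concern.** If credibility is to be set aside as a competing cause of an arm effect, it should be measured before the interventions can have changed it. Here it is measured after exposure. A participant who feels better after several sessions is likely to rate the program as more credible, and one who is bored or disappointed as less so. The rating then partly results from treatment.

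The error can go either way. Early benefit can create an arm difference where initial belief was equal, and a poor first week can hide one that existed at the start. The Control Group Description gives the sham the task of controlling for expectation, and this questionnaire is the only listed measure of whether it does so. The interpretation of any efficacy signal passed on to the definitive trial is what is at stake.

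**Working it through.** **1. Exposure before the rating.** Enrollment is day 0, first use is day 1 and the rating is at day 7, so exposure is 7 − 1 = 6 days. As a share of the 4-week course, 6/28 = 21%. At 4 to 6 sessions of about 10 minutes, that is 40 to 60 minutes of use.

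**2. Whether a response by then is plausible on the article's own terms.**
- Background and Rationale cites positive effects from web-based mindfulness programs lasting as little as 3 days.
- The Control Group Description reports that the comparator game did not reduce stress or improve well-being in an earlier study, so early benefit would be expected mainly in one arm.
- The Figure 2 legend says participants in both arms can see in the app how their sessions affected their well-being.

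**3. The plan's own credibility figures.** The inputs are a red limit of 0.50 and a green limit of 0.70 (Table 2), and 90% power (Statistical Power). One-sided alpha 0.05 is assumed because the article states none.
- Uncorrected: n = [(1.645 × √(0.5 × 0.5) + 1.282 × √(0.7 × 0.3)) / 0.2]² = 49.7.
- With continuity correction: n = (49.7/4) × [1 + √(1 + 2/(49.7 × 0.2))]² = 54.6, so 55, as stated.
- Power at n = 70: Φ[(0.2 − 1/140 − 1.645 × 0.5/√70) / √(0.21/70)] = Φ(1.73) = 95.8%, as stated.

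Neither figure depends on when the rating is taken.

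**4. How large an arm difference early benefit alone can produce.** Initial credibility is set equal in both arms. The week-1 rating is b × experience + √(1 − b²) × everything else, all in SD units, and experience is shifted by d in the mindfulness arm. The expected arm difference in the rating is then b × d. The values of b and d are assumptions; the article gives none. The table shows the expected difference and the share of 20,000 simulated trials with two-sided P<.05, at 35 per arm.

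| Week-1 benefit d | b = 0.3 | b = 0.5 | b = 0.7 |
|---|---|---|---|
| 0 | 0.00; 5.1% | 0.00; 5.4% | 0.00; 5.1% |
| 0.3 | 0.09; 6.4% | 0.15; 9.3% | 0.21; 13.7% |
| 0.5 | 0.15; 9.5% | 0.25; 17.9% | 0.35; 30.4% |
| 0.8 | 0.24; 16.8% | 0.40; 38.2% | 0.56; 63.5% |

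At 28 per arm (35 × 0.8, for the stated 20% loss) the range for d from 0.3 to 0.8 is 6.5% to 54.2%.

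**5. What similar ratings would show.** The 95% half-width for an arm difference is 1.96 × √(2/n): 0.47 SD at 35 per arm and 0.52 SD at 28 per arm. A null result would leave moderate differences open.

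**The case against.** The strongest defense is that week 1 is a reasonable time. Families are blinded to the purpose and expected results of the interventions and to the other arm (Methods for Protecting Against Bias), so a rating before use rests on little information. For the Table 2 progression criterion, a rating informed by some use is appropriate. This stands, and the week-1 rating should be kept for that purpose.

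Several stronger readings are tempting but are not supported:
- *That the week-1 rating is useless for the between-arm question.* Similar ratings would count, weakly, against differential credibility. Only an observed difference becomes ambiguous.
- *That the plan would credit a real effect to credibility.* No credibility-adjusted or mediation analysis is described. The Statistical Analysis section plans means, SDs and pre-post correlations for secondary outcomes, and the covariates named for the neuroimaging models do not include credibility. Misattribution is a risk of interpretation.
- *That anyone who stops in week 1 is missed.* Follow-up questionnaires are completed on REDCap (Follow-Up Procedures) and coaches send reminders (Coaching), so a person who stops using the app can still answer. Only those lost to follow-up are missed.

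The in-app mood and stress readings, collected in both arms from first use, would help to judge early response. They reduce the ambiguity but cannot replace an initial rating. It is also fair that 6 of 28 days measures elapsed time and not bias, and that the simulated range rests wholly on assumed inputs.

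**Conclusion.** The point holds in limited form. The single rating comes after about 6 days of use, so an observed arm difference would combine initial belief with early response, and the two could not be separated without an earlier value. The use stated in footnote a is therefore not served by the timing that the same footnote fixes.

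Under the assumed inputs the effect runs from negligible (0.09 SD, significant in about 6% of trials) to serious (0.56 SD, about 64%), and the week-1 rating alone could not show which applies. A reader might infer that the feasibility decision on credibility is compromised. It is not: the midpoint criterion, n of 55 and power of 95.8% are unaffected. Because this is a feasibility trial with only an exploratory efficacy signal, the change is a cheap improvement and not a condition for validity.

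**What to change.** For participants still to be enrolled, add the 6-item questionnaire once at the day-1 contact, after the assigned intervention has been described and before the app is first used. If that is impractical, give it straight after the first session at the latest. Slight contamination then has to be accepted, because the app can already show a session's effect. Use this early rating for the between-arm comparison of credibility and expectancy, and keep the week-1 rating for Table 2.

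For participants without the early rating, qualify the statement in footnote a: a week-1 arm difference may reflect early response, and similar ratings give only limited reassurance. If recruitment is too far advanced (data collection was expected to finish by September 2024), make this qualification now and move the rating earlier in the definitive trial.

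The cost is one extra 5-minute form per participant (the time given in Table 3), at a contact where day-1 questionnaires are already completed by phone or REDCap, with no added staff. The drawback is that the early rating rests on less experience of the app.
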